##### Missing Data and Dropouts

Although treating participants lost to follow-up as “not abstinent” has been a widely used analytical strategy in smoking cessation studies, some researchers have pointed to potential problems with this “intent to treat” approach, especially when comparing treatment arms with differential dropout rates [55]. Thus, we will conduct sensitivity analyses to test for treatment differences assuming different missing data mechanisms. For example, we will consider a multiple imputation approach based on smoking-related patient characteristics at baseline as well as demographics to account for potential missing-at-random mechanisms. We also will explore pattern-mixture and selection models to account for potential (and likely) missing-not-at-random mechanisms [56]. Similar findings based on these sensitivity analyses will strengthen our study conclusions.

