#### Primary Outcome

The primary outcome is smoking status 12 months post enrollment. Abstinence is defined as biochemically confirmed self-reported 7-day point prevalence abstinence with expired CO <6 ppm [54]. Secondary outcomes include 3- and 6-month biochemically confirmed abstinence. We will consider several other common outcomes, such as self-reported abstinence, length of abstinence, and number of quit attempts.

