### Data Analysis Plan

#### Aim 1: Conduct an RCT to Evaluate the Efficacy of AM for Cambodian People With HIV Who Smoke

##### H1: At the 12-Month Follow-Up, Smoking Abstinence Will Be Higher in the AM (vs SC) Group

The primary outcome is biochemically verified 7-day point prevalence abstinence at the 12-month follow-up. The primary abstinence analysis will be intention-to-treat, with patients who do not complete the follow-up assessments considered to be smokers; however, we will explore other approaches for dealing with missing data (see Missing Data and Dropouts below).

To estimate the effect of AM on abstinence rates while accounting for the potential clustering of participants recruited from multiple clinic sites, we will use generalized linear mixed models (GLMM) analyses in which intervention groups (AM vs SC) will be estimated as a fixed effect, while the clinic will be modeled as a random effect nested within the treatment condition. Specifically, log binomial mixed models will be used to estimate the relative risk of quitting in the AM (vs SC) group. Although groups should be similar in baseline characteristics due to randomization, we will explore models that control for any demographic or clinical variables that differ between groups at baseline. We will also use GLMM to examine changes in abstinence rates over time while accounting for relevant baseline covariates. Similar GLMM or methodology, as appropriate for each outcome variable, will be used to examine other smoking-related variables, such as continuous abstinence, prolonged abstinence, and quit attempts. Statistical analyses will be performed using SAS (version 9.4; SAS Institute, Inc).

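### The only missing-at-random sensitivity analysis named imputes 12-month abstinence from baseline data and demographics, and omits the 3- and 6-month CO-verified status collected in both arms

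*Protocol article*

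**What the plan says.** Under H1 in the Data Analysis Plan, the protocol article defines the endpoint: "The primary outcome is biochemically verified 7-day point prevalence abstinence at the 12-month follow-up". The primary analysis has "patients who do not complete the follow-up assessments considered to be smokers".

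Missing Data and Dropouts explains why that rule needs checking: it can mislead, "especially when comparing treatment arms with differential dropout rates". The first check is introduced as an example of what will be considered. It is a "multiple imputation approach based on smoking-related patient characteristics at baseline as well as demographics", and its stated purpose is to cover dropout that is missing at random. The next sentence adds a second kind: "We also will explore pattern-mixture and selection models to account for potential (and likely) missing-not-at-random mechanisms". The section closes by saying that agreement across these analyses would strengthen the conclusions.

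Interim smoking status is available in both arms. Under Primary Outcome, "Secondary outcomes include 3- and 6-month biochemically confirmed abstinence", and Table 1 lists smoking status and expired CO at the 3-, 6- and 12-month clinic visits. Weekly smoking status is not available in both arms: under Brief Weekly Smartphone Assessments, SC participants answer questions about diet.

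**The concern.** Missing at random always means at random given the variables in the model. Given baseline data alone, it requires that two participants with the same baseline profile, one verified abstinent at month 6 and the other seen smoking, have the same chance of being lost by month 12, or that the month-6 result says nothing about month 12. Neither is plausible in a cessation trial. Under the predictors named, a participant who was smoking at month 6 and then disappeared is imputed much like the average completer with the same baseline profile.

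At stake is whether this analysis is informative about the problem the section itself raises, namely dropout that differs between arms. If dropout among people still smoking differs by arm, the imputed relative risk moves away from the truth. Agreement or disagreement with the primary result would then partly reflect the omitted predictor.

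**Working it through.** The article gives no 12-month abstinence rates, dropout rates or power figures for the trial, so there is no planned figure to reproduce. All rates below are assumptions chosen to show direction and size.

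**Set-up, per arm.** Let q be the proportion abstinent at 6 months, and let d1 and d2 be 12-month dropout among 6-month abstainers and non-abstainers. Assume 12-month abstinence of 60% if abstinent at 6 months and 8% if not, with dropout depending only on arm and 6-month status.

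- True rate = 0.60q + 0.08(1 − q).
- Imputation by arm from uninformative baseline data tends to the completer rate: [0.60q(1 − d1) + 0.08(1 − q)(1 − d2)] / [q(1 − d1) + (1 − q)(1 − d2)].
- Missing = smoking gives the numerator of that fraction.

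**Truth.** With q = 0.30 in the automated messaging (AM) arm and 0.20 in SC: 0.236 / 0.184 = RR 1.283.

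**Worked case: d1 = 8% in both arms, d2 = 30% AM and 20% SC.**
- AM: (0.30×0.92×0.60 + 0.70×0.70×0.08) / (0.30×0.92 + 0.70×0.70) = 0.2048 / 0.766 = 0.2674.
- SC: (0.20×0.92×0.60 + 0.80×0.80×0.08) / (0.20×0.92 + 0.80×0.80) = 0.1616 / 0.824 = 0.1961.
- Baseline-only imputation: RR 1.363. Missing = smoking: 0.2048 / 0.1616 = 1.267.

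**Range (d1 = 8% throughout):**

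| Dropout of 6-month smokers, AM / SC | True RR | Baseline-only imputation | Missing = smoking |
|---|---|---|---|
| 30% / 20% | 1.28 | 1.36 | 1.27 |
| 35% / 15% | 1.28 | 1.45 | 1.23 |
| 20% / 30% | 1.28 | 1.21 | 1.36 |
| 25% / 25% | 1.28 | 1.28 | 1.31 |
| No effect (q = 0.20 in both), 30% / 20% | 1.00 | 1.06 | 0.96 |
| No effect, 35% / 15% | 1.00 | 1.13 | 0.92 |
| No effect, 15% / 35% | 1.00 | 0.88 | 1.08 |

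At equal 25% dropout the relative risk is right, but both rates are about 2 points too high: 25.9% against 23.6% in AM, and 20.2% against 18.4% in SC.

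**Second set of assumptions.** Take 6-month abstinence of 25% AM and 15% SC, and 12-month abstinence of 70% or 8% by 6-month status. The truth is 23.5% against 17.3%, a difference of 6.2 points (RR 1.36).
- Dropout 20% regardless of status: no bias.
- Non-abstainers 25% and abstainers 10%, the same in both arms: 6.9 points, RR 1.37.
- Non-abstainers 30% and abstainers 10% in AM only, SC 20% throughout: 9.3 points, RR 1.54.
- The same pattern in SC only: 4.0 points, RR 1.21.

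**Simulation** (400 per arm, 20 imputations, Rubin's rules, a weak baseline predictor) of the AM-only pattern with no true effect: baseline-only imputation gave a mean difference of 3.0 points and 12% false positives. With 6-month status added, these were 0.05 points and 4%. With the effect present, the difference was 6.5 points in full data, 9.5 with baseline-only imputation and 6.6 with 6-month status added.

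**The case against.** The strongest reply is that the sentence is an illustration of something to be considered. A reader might infer that the trial will use baseline data only and will ignore its interim results. The text says neither: it excludes nothing, and a fuller variable list may stand in a document not shown. That stands, and limits the point to the predictors the article names. It does not remove it, because the article states what the imputation is based on and leaves out the obvious predictors.

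A reader might also infer that this imputation is the safeguard for the primary result. It is not. Pattern-mixture and selection models are planned too, and the section calls missing-not-at-random dropout likely. The model of abstinence over time under H1 uses the repeated measures, although it is not presented as a missing-data analysis. The primary result does not depend on the imputation.

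The bias is also conditional. With similar dropout patterns in both arms, the relative risk, which is the planned effect measure, is nearly unbiased. And in the unequal-dropout rows of the table, baseline-only imputation and missing = smoking fall on opposite sides of the truth, so the divergence would warn rather than falsely reassure. This stands for those inputs but is not general: in the second set, with the AM-only pattern, both err upward (RR 1.54 and 1.44 against 1.36; with no effect, 1.13 and 1.06 against 1.00).

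Finally, the complete correction seen in the simulation is built in: 6-month status is known for everyone and dropout depends on nothing else. That objection is sound and is reflected in the verdict.

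**Conclusion.** The point holds as a weakness in the stated inputs of one sensitivity analysis, the only one the article names for missing-at-random dropout. It is minor to moderate.

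The size depends on how unequal the status-related dropout is. In the first set of assumptions with a true RR of 1.28, unequal dropout moves the imputed value to between 1.21 and 1.45; with no true effect, to between 0.88 and 1.13. Where the pattern is alike in both arms, the error in the relative risk is nil or small, and what remains is overstated abstinence in both arms if smokers drop out more. These figures assume imputation by arm and baseline variables that say little or nothing about interim status. More informative baseline data would shrink them.

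The calculations do not show that the primary conclusion is biased by the imputation, or that adding interim status would cure all dropout bias. Participants also missed at 6 months, and dropout driven by unobserved relapse, are outside them.

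**What to change.** State in Missing Data and Dropouts (and in the analysis plan, if it does not already say so) that the imputation model will include treatment arm, or be run separately by arm. Its predictors should be observed 3- and 6-month abstinence, both self-reported and CO-verified, together with sex, clinic and baseline smoking variables. Missing 3- and 6-month values should be imputed jointly with the 12-month outcome.

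Leave weekly smoking reports out of the model, since SC has no counterpart to them. Keep the pattern-mixture and selection models: the change makes the missing-at-random assumption more credible, but does not deal with dropout that is missing not at random.

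The cost is a sentence or two of plan wording and slightly more programming. No new data are needed, and the primary analysis is unchanged. It should be settled before the final analysis.

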#### Aim 2: Conduct an Economic Evaluation to Compare the Cost-Effectiveness of the 2 Smoking Cessation Interventions (AM vs SC)

##### H2: AM Will Be More Cost-Effective Than SC

Information on costs and cost-effectiveness is especially important for decision makers in LMICs, as these countries are particularly resource constrained. Evidence of cost-effectiveness is critical for our partners in government agencies to implement and ultimately to scale up the AM program at ART clinics throughout Cambodia. To facilitate decision-making of stakeholders in the public sector, the cost-effectiveness analysis (CEA) will be conducted from the perspective of the governmental service providers.

##### Measures of Costs and Collection of Cost Data

For AM and SC, the costs associated with implementation will come from 4 sources: study personnel, capital costs, production of materials, and distribution of materials. If existing resources are used without charge (eg, office space or computers), we will estimate these costs, given that they would be required for implementation. We will not include the cost of the smartphones because once the efficacy of AM is established, implementation will capitalize on the wide availability of mobile devices in the community and will not involve the distribution of these devices.

##### Measures of Effectiveness

Two commonly used measures of effectiveness, number of quitters and years of life saved (YOLS) [57], will be used to compare with other CEAs of smoking cessation interventions published in the literature. The number of quitters in each arm will be extracted from the 12-month abstinence assessment. We will extrapolate from abstinence to YOLS using a published algorithm that models YOLS per quitter [58]. We will revise the algorithm using more current estimates of age-specific smoking-attributable deaths from tobacco [59], adjusting for reduction in survival for people with HIV. We also will include quality-adjusted life years, which will be calculated based on the five-level EQ-5D (EQ-5D-5L). The EQ-5D-5L is the latest version of the EQ-5D health–related quality of life questionnaire and has been translated into Khmer [53].

##### Analysis

We will summarize findings from the CEA in terms of the incremental cost-effectiveness ratio, calculated as the difference in mean costs between the AM and SC treatments divided by the difference in mean effectiveness between the 2. The incremental cost-effectiveness ratio estimates additional resources needed to achieve an increase in 1 unit of effectiveness and is compared with a commonly published threshold value, which is 3 times the gross domestic product per capita for LMICs according to WHO recommendations [60]. We will assess both short-term and long-term economic impacts of the interventions. To obtain the 95% CIs, we will apply nonparametric bootstrapping methods to the person-level data [61]. We will conduct 1-way sensitivity analyses to examine the impact of alternative measures of cost and outcomes or key assumptions. We will then apply the Bayesian approach to construct the cost-effectiveness acceptability curve and conduct probabilistic sensitivity analysis [62,63]. We will conduct the Bayesian analysis using WinBUGS (BUGS Project), with costs modeled as a gamma or lognormal distribution and abstinence as a binomial distribution [64].

#### Aim 3 (Exploratory): Explore Potential Mediators and Moderators Underlying the Associations Between Treatment Group and Abstinence

We will explore potential mediators and moderators underlying the associations between treatment group and abstinence, as informed by the PBM. We will compare the magnitude of the mediated effects of AM treatment on the outcome of abstinence. Potential mediators include NRT adherence, nicotine withdrawal, motivation, self-efficacy, social support, coping with stress, and positive or negative affect. We also will investigate moderators of the relationship between the treatment group and abstinence to determine the types of participants who may benefit most from AM treatment. We will explore biological sex, HIV stage (as measured by CD4 count and viral load), ART adherence, presence and treatments of common comorbidities (eg, tuberculosis), illicit substance use, and nicotine dependence level as possible moderators. Although we anticipate a small proportion of women in our study, we will make every effort to explore the potential moderating effect of biological sex on the association between treatment arm and abstinence.

## Results

Participant recruitment commenced in January 2023, with all data expected to be collected by the end of 2025. Frequent data analyses to monitor participant performance will occur during the recruitment and follow-up periods, with final data analysis to occur after data collection concludes.

## Discussion

This project capitalizes on a strong, collaborative partnership among researchers at Moffitt Cancer Center, University of Oklahoma Health Sciences Center, The University of Texas MD Anderson Cancer Center, and 3 national governmental agencies that are comprehensively responsible for HIV/AIDS control and care in Cambodia. The investigative team consists of US and Cambodian experts in tobacco, HIV, economic evaluation, mHealth, and health care administration. If our findings indicate that AM is efficacious and cost-effective, our collaboration with influential Cambodian governmental agencies will facilitate wide-scale implementation to HIV clinics across the country. Thus, the project has the potential to transform HIV care delivery throughout the country and to reduce tobacco-induced morbidity and mortality significantly.

Cigarette smoking among people with HIV represents a global public health problem. This issue is even more striking in Cambodia due to a high smoking prevalence in people with HIV and a lack of cessation treatment efforts for this population. Available data (ie, high smartphone ownership rates in Cambodia and high ART coverage) suggest that our approach, which involves recruiting participants from ART clinics and using smartphones to deliver a cessation intervention, represents an ideal and highly feasible way to address this public health problem. Existing data also suggest that Cambodians are receptive to mHealth interventions, and our promising data from the EndIT-Pilot support the feasibility, acceptability, and preliminary efficacy of our approach [20]. This project will provide valuable long-term efficacy data for the AM intervention in a large population of Cambodian people with HIV. Given AM’s potential as a feasible, scalable, highly affordable, and cost-effective standalone intervention, the proposed work has the potential to transform HIV care delivery throughout Cambodia. Sustainability and widespread adoption potential are further enhanced by the direct involvement of Cambodian governmental health agencies. In addition, AM could potentially be integrated with other mHealth services for HIV/AIDS care, such as ART adherence and tuberculosis prevention or treatment. AM also has the potential to be broadly adapted for other populations in Cambodia and other LMICs to address the critical need for tobacco treatment. Finally, very little evidence to support the efficacy and cost-effectiveness of smartphone-based tobacco cessation treatment is available in LMICs [65], and it is largely unknown whether effective cessation interventions from high-income countries are transferable and applicable to LMICs. Therefore, our work will help to answer critical questions including what types of tobacco cessation interventions can be effectively introduced to LMICs and whether this type of mHealth intervention is more cost-effective than alternative treatments in settings with low-cost mobile phone services.

## Appendix

Multimedia Appendix 1 Peer review reports from the National Cancer Institute Special Emphasis Panel on Tobacco Use and HIV in Low and Middle Income Countries.

## Abbreviations

AM: automated messaging
ART: antiretroviral treatment
CASI: computer-assisted self-interview
CEA: cost-effectiveness analysis
CO: carbon monoxide
GLMM: generalized linear mixed model regression
IRB: institutional review board
LMICs: low- and middle-income countries
mHealth: mobile health
NRT: nicotine replacement therapy
PBM: Phase-Based Model
RCT: randomized controlled trial
SC: standard care
WHO: World Health Organization
YOLS: years of life saved
